#### **Treatment integrity**

To check the treatment integrity, during the implementation and period of data collection, process indicators will be assessed. These indicators will report the degree of completion of the eHealth modules (registered by research assistants in the research database), number of completed ROM measurements (data extraction from electronic patient records) and the extent of using peer support (registered by peers themselves).

#### **Sample size calculation**

This study is designed to detect a medium effect size of  $d = 0.5$  on the primary outcome parameter between the intervention and control group. A significance level set at  $\alpha = 0.05$  and 65 patients per arm will yield a power of 0.80 [67]. Due to the cluster-randomisation at team level, we will calculate the effective sample size with an intra cluster correlation coefficient (ICC). The ICC is a measure of relatedness of responses within a cluster [68]. When adjusting for clustering within the matched pair teams of each department we expect an  $ICC = 0.01$ . Using the following formula [68]: Design Effect (DE) =  $1 + (m-1) ICC$  (0.01) ( $m$  = number of subjects in a cluster), the sample size needs to be 77 patients per arm. We expect about 10% of the participants to drop out of the study. This requires an

initial inclusion of 88 patients per arm, which means that in total 176 patients and on average 44 patients per centre (22 patients per intake-team per arm) will need to be included.

### Statistical analyses

The data will be analysed according to the intention-to-treat principle. In addition, a completer case analysis will be performed.

Descriptive analysis will be conducted to describe patients' characteristics (age, gender, educational level, diagnosis, SQ-48 (ROM) score at T0, motivation for treatment at T0, previous treatment and length of waiting) to check the similarity between the intervention and control group. In addition, treatment integrity (degree of completion of the eHealth modules, number of completed ROM measurements and the extent of using peer support) will be described.

Due to the cluster randomisation, the hypotheses will be tested using multi-level analysis [45], which is also a flexible statistical method in handling missing data [69]. We assume a three level structure: clusters (departments), patients and multiple measurements over time (within patients) [70].

The patients' and clinicians' views on the Shared Decision Making process (SDM-Q-9) and Decisional Conflict (VAS) will be compared using independent t-tests.

Analyses will be conducted using SPSS 19.0 and MLwiN 2.21. Reporting of the results of the study will be in accordance with the CONSORT statement 2010 (extension cluster randomised trials).

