This study will be conducted in four outpatient departments of a specialised mental health institution GGz Breburg, located in the southern part of the Netherlands. Annually, more than 14.000 patients are treated by about 2000 employees at GGz Breburg. The digital intake approach will be being tested among various diagnostic groups (patients with depression, anxiety and personality disorders as their primary diagnosis). Two of the participating departments are specialised in treating patients with depression and anxiety disorders; each operating in a separate geographical catchment area. The other two departments are specialised in personality disorders and are active in separate catchment areas. The four participating departments are each divided into two teams of clinicians who perform intakes (Fig. 1). Each team of intake-clinicians have their own multidisciplinary team consultation, in which treatment policy at the patient level is discussed and checked. Due to the matched pair design at the level of intake-teams within each department, in total four intervention and four control teams participate. In accordance to the sample size calculation (see section

sample size, page 18) 176 patients will be included (88 in the intervention and 88 in the control teams), with an average of 44 patients per department (22 intervention and 22 control).

Inclusion and exclusion

Patients from the participating departments will be invited for participation in this study if a) a full intake is planned and b) when they are fluent in Dutch. Patients who meet these criteria will be asked for written informed consent. Patients will be excluded form the study if they do not receive a full intake and do not have adequate Dutch language skills (verbal and written).

Randomisation and blinding

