A cluster randomised design at the level of intake-teams and participation of intake-teams in separate multidisciplinary consultations will serve to limit contamination effects between intervention and control groups [45]. The pairs of intake groups within a department are randomly assigned to either the experimental or control condition (matched pairs). The matched teams within each department perform intakes for a similar population of patients in a similar geographic catchment area and have similar personnel. Randomisation of the intake-teams is conducted by an independent researcher, using a syntax in SPSS, which allocates the matched pairs to the control (code 0) or intervention group (code 1). To reduce bias, data collection for this study will be carried out by research assistants, independent of the principal investigator and treatment, with self-report instruments completed by both patients and clinicians. This results are not visible at patient level during intake and treatment. Only the outcome parameters no-show, drop-out and clinical outcome (ROM) will be collected in the context of treatment. As is common practice in cluster randomised RCTs, propensity analyses will be performed at the analytical stage to correct for possible biases in the randomisation process [45].

During inclusion, while informing patients and asking them for written informed consent, the research assistants are blinded for the study arm. The questionnaires

[figure not shown]

Fig. 1 Participating departments and intake teams

are based on self report and hence do not require assessment by a research assistant. Due to the randomisation at the team level and the nature of the intervention, blinding of the clinicians and patients is impossible.

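### The analysis model names departments as its only cluster level, although intake teams were randomised; with no team term, the 5% test runs at about 7 to 7.5% at the protocol's own ICC

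*Protocol*

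**What the plan says.** On the design, the protocol is consistent. Randomisation and blinding describes "A cluster randomised design at the level of intake-teams" and adds: "The pairs of intake groups within a department are randomly assigned to either the experimental or control condition (matched pairs". Participants and setting gives the count: "in total four intervention and four control teams participate", which is one team of each arm in each of the four departments. Sample size calculation works at the same level: "Due to the cluster-randomisation at team level, we will calculate the effective sample size with an intra cluster correlation coefficient (ICC"). The value used is introduced with "When adjusting for clustering within the matched pair teams of each department we expect an" ICC of 0.01, and the enrolment target is "22 patients per intake-team per arm".

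Statistical analyses changes level. It says the hypotheses will be tested by multilevel analysis because of the cluster randomisation, and then fixes the levels: "We assume a three level structure: clusters (departments), patients and multiple measurements over time (within patients) [70"]. The team does not appear. No other section adds a team level, an arm effect that varies by department, a cluster-level test or a small-sample correction. The propensity analyses in Randomisation and blinding are aimed at imbalance between the arms and do not represent correlation within teams.

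**The concern.** The protocol treats team variance as real when it sizes the trial and leaves it out of the model when it tests. The department level is no substitute. Because both arms occur in every department, whatever a department's patients share is subtracted out of the arm difference. What the patients of one team share is not subtracted, because a team belongs wholly to one arm.

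If that component is left in the residual, the model treats it as if it averaged out over some 154 independent patients (77 per arm), when it averages out over only four teams per arm. Confidence intervals are then too narrow, and an ordinary difference between teams of clinicians can be read as an effect of the new intake. This applies to the primary analysis of decisional conflict and to every secondary outcome tested with the same model.

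**Working it through.** **Inputs.** From Sample size calculation: d = 0.5 (SD set to 1), alpha 0.05, power 0.80 with 65 per arm, ICC 0.01, 77 per arm after the design effect, 10% dropout, 88 per arm enrolled, 22 per team. From Participants and setting: four departments with two teams each. Sidedness is not stated; two-sided is assumed because it reproduces the stated 65.

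**1. The plan's own figures.** A two-sided t-test at d = 0.5 needs 64 per arm, and 65 gives power 0.81. With design effect DE = 1 + (m − 1) × ICC and the team as cluster (m = n/4), solving n = 65 × DE gives n = 65 × 0.99 / (1 − 65 × 0.01/4) = 76.8, the stated 77. With the department as cluster (m = n/2), n = 65 × 0.99 / (1 − 65 × 0.01/2) = 95.3. So 77 is obtained only if the team is the cluster. Dividing 77 by 0.9 gives 86, close to the stated 88.

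**2. True variance of the arm difference.** With ICC ρ between teams within a department (total variance 1 apart from the department component) and m analysed patients per team, a team mean has variance v = ρ + (1 − ρ)/m. Department effects cancel within each pair, so the mean of the four within-department differences has variance 2v/4 = v/2.

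At ρ = 0.01 and m = 77/4 = 19.25: v = 0.01 + 0.99/19.25 = 0.0614.

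**3. Variance reported by a model with a department intercept only.** The pooled residual has 8m − 5 df and expectation

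s² = [8(m − 1)(1 − ρ) + 3mv] / (8m − 5) = (144.54 + 3.55)/149 = 0.994.

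The model uses s²/m = 0.0516 where the true value is 0.0614.

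**4. Consequence.** True SE / model SE = √(0.0614/0.0516) = 1.091, so the model SE is 1 − 1/1.091 = 8.3% too small. Two-sided error = 2 × P(Z > 1.96/1.091) = 7.2%. At m = 22 (no dropout) the ratio is 1.103, the SE is 9.4% too small and the error is 7.6%.

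| Team ICC | Status | SE ratio (m = 19.25) | Error, m = 19.25 | Error, m = 22 |
|---|---|---|---|---|
| 0 | no team variance | 1.000 | 5.0% | 5.0% |
| 0.0025 | assumed: three quarters of 0.01 shared by department | 1.023 | 5.5% | 5.6% |
| 0.005 | assumed: half of 0.01 shared by department | 1.046 | 6.1% | 6.3% |
| 0.01 | protocol's value | 1.091 | 7.2% | 7.6% |
| 0.02 | assumed | 1.176 | 9.6% | 10.2% |
| 0.05 | assumed | 1.405 | 16.3% | 17.8% |

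Simulation (200,000 runs per setting, one value per patient, equal teams, assumed department variance 0.02, critical value 1.96) gave 7.5% at m = 19 and 7.8% at m = 22 for ICC 0.01. A paired t-test on the four within-department differences (3 df) stayed at about 5% at every ICC tried.

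**5. Power of the corrected test.** At ICC 0.01 and m = 19.25, SE = √(0.0614/2) = 0.175 and the noncentrality is 0.5/0.175 = 2.85. The critical value of t with 3 df is 3.18. The noncentral t gives power 0.50; the simulation at m = 19 gave 0.49. Even at ICC 0 the same test has power of only 0.56, so most of the shortfall from 0.80 comes from having four pairs and not from the ICC.

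**The case against.** The strongest reply is that the model is not fully specified. The protocol lists levels; it does not say which coefficients are random or which test and degrees of freedom apply. Because each department holds one team per arm, an arm effect allowed to vary randomly across departments would carry the team variance within the same three levels. The parenthesis naming departments may also be loose wording, since the Discussion uses cluster level to mean the teams within each department. Part of this stands: the size calculated above is conditional on no such term being fitted, and the document names no particular test. It does not remove the point, because no such term is in the text and the cluster level that is named is the wrong one.

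The second reply concerns size. The protocol does not say whether its ICC of 0.01 lies wholly between teams within a department or is partly shared by the department. Any shared part cancels through the matching, and the error is then nearer 5.5 to 6%. This stands.

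A reader might go further and infer that the 5% level is certainly lost, or that the error is 10% or more. The documents do not support either reading. The first ignores the dependence on the ICC and on a random-intercept model; the second needs ICCs of about 0.02 or more, which appear nowhere in the protocol.

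**Conclusion.** The point holds as an explicit inconsistency in the protocol: trial and sample size are built on intake teams, while the stated analysis clusters on departments. Since the levels are written out, this is a wrong statement and not a detail left for a statistical analysis plan.

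The consequence at the protocol's own ICC is modest but real: an SE about 8 to 9% too small and a two-sided error of about 7 to 7.5%. This assumes that all of the 0.01 lies between teams within a department, that team sizes are about equal, that only a department intercept is fitted and that a large-sample critical value is used. The rates of about 9 to 10% at ICC 0.02 and 16 to 17% at ICC 0.05 show sensitivity to an assumption and are not what the protocol implies. The inflation vanishes only if the team ICC is zero, which the sample size calculation does not assume. The text should be corrected because it governs the primary test.

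**What to change.** In Statistical analyses, replace departments as the cluster level with the intake team as a random level: measurements within patients within teams. Add department as a fixed effect for the matched pair, and test the arm effect with small-sample degrees of freedom that reflect eight teams, for example Satterthwaite or Kenward-Roger.

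A paired t-test on the four within-department team differences (3 df) is a simple alternative. It is close to the mixed model but not always identical: they agree when the data are balanced and the estimated team variance is above zero. With eight teams and an ICC near 0.01, zero estimates will be common, so the plan should say what is done then.

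The edit to the text is short, but it is not free. Confidence intervals widen, and power with the 3-df test at d = 0.5, ICC 0.01 and about 19 analysed patients per team is about 0.50. The 0.80 in Sample size calculation makes no allowance for so few clusters and should be restated together with the model.

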### Study flow

Patients who are referred to one of the participating departments, are invited for an intake consult. Patients

who are planned for an intake consultation with a clinician of the intervention group, are assigned to the intervention team and will get the new eHealth intake automatically. Patients who have this first appointment with a clinician of the control group, are assigned to the control group and will follow the intake as usual. In addition, both groups of patients, who follow the new intake process and the intake as usual, will be invited to participate in the evaluation research consecutively. Research assistants inform all patients (who meet the inclusion criteria) about the research, ask them to participate in the study and obtain written informed consent.

Three measurement points will be scheduled (see Table 2): baseline assessment (T0) and two measurements (T1, T2) after the intake (T1 = two weeks after intake, T2 = two months after intake). Because only T1 and T2 contains additional questionnaires for this research, written informed consent will be asked during the first face to face appointment, just before T1. Patients who give informed consent for the research, are completing self-report questionnaires organised by independent research assistants. In addition to T1, clinicians answer questions about shared decision making regarding their patients. Patients and clinicians who participate in the study, receive a request by email to complete the questionnaires. If necessary, one week later they get a reminder by email. After nine and fourteen days the research assistant calls patients who have not yet

**Table 2** Measurement points

| Assessment/Questionnaire                                                                                                                    | Baseline (T0) | 2 weeks after intake (T1) | 2 months after intake (T2) |
|---------------------------------------------------------------------------------------------------------------------------------------------|---------------|---------------------------|----------------------------|
| Primary Outcome Parameter                                                                                                            |               |                           |                            |

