### Primary outcome measure

The primary outcome measure is the degree of decisional conflict a central determinant of decision making, which is defined as 'personal uncertainty about which option to choose' [55, 56], will be measured with the translated Decisional Conflict Scale (DCS) [18, 55]. The DCS is a self-report questionnaire comprising sixteen questions about personal perceptions of: uncertainty in choosing options, modifiable factors contributing to uncertainty, effective decision making such as feeling the choice is informed, values-based, likely to be implemented and expressing satisfaction with the choice [55]. Each item is measured on a 5-point Likert scale (0 = strongly agree to 4 = strongly disagree). Besides the total score, the DCS has the following five subscales: uncertainty, informed, values clarity, support and effective decision. To calculate the total and subscale scores the item scores will be averaged and multiplied by 25. The

[figure not shown]

scores thus range from 0 (no decisional conflict) to 100 (extremely high decisional conflict).

The psychometric properties of the English version of the DCS are adequate. Test-retest reliability (0.81) and Cronbach alpha (0.78) are high. The scale correlates to related constructs (knowledge, regret, discontinuance) and discriminates between groups who make and delay decisions (construct validity). DCS is responsive to change between different decision supporting interventions. The predictive validity of the DCS is also demonstrated [44, 55, 56].

To compare the degree of decisional conflict (or agreement) between patients and clinicians about the decisions made, at T1 both patients and clinicians fill out a Visual Analogue Scale (VAS).

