  - 5) Patient-Doctor Relationship Questionnaire (PDRQ-9) [64].

The SDM-process will be measured with the Shared Decision Making-Questionnaire-9 (SDM-Q-9) [61, 62], which has Dutch versions for patients and clinicians [18, 63]. Both versions ask the patient and clinician first to enter the health problem the consultation was about and which decision was made. The questionnaire continues with nine items about the steps in the SDM process, scoring at a 6-point Likert scale that ranges from 0 (completely disagree) to 5 (completely agree). A total score can be calculated by summing the scores of all items. A high score indicates more SDM. The SDM-Q-9 shows a high reliability [61, 62]. The available results about the factorial validity are also positive [61, 62]. The psychometric testing of the Dutch version of the SDM-Q-9 [63] demonstrated good acceptance, internal consistency, and acceptable to good convergent validity of the versions for patients and physicians. Patients will be asked to complete the SDM-Q-9 at T1 and T2. At T1 clinicians will complete the same questions regarding the consultations with their patients.

The PDRQ-9 will measure the working alliance. The PDRQ-9 consists of 9 items and measures the therapeutic aspects of the clinician-patient relationship from a patient point of view. The items focus on the empathic style and availability of the clinician and are answered on a 5-point Likert scale (1 = not at all appropriate to 5 = totally appropriate). Two sample items are: 'My clinician understands me' and 'My clinician and I agree on the nature of my medical symptoms'. A mean score of all nine items is calculated. A higher score means more satisfaction about the relationship. The psychometric quality of the Dutch PDRQ-9 shows good internal consistency, adequate test-retest reliability and the ability to discriminate between patient groups [64].

Next the patients' adherence to treatment will be investigated. Adherence can be defined as the extent to which the patient's behaviour concur with the advice of the clinician [9]. In this study adherence is operationalised as the number of missed appointments (no-shows) and patients who do not want to proceed with treatment

(early treatment drop out). These data will be extracted from the electronic patient records.

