A second strength is that the additional data collection for this research is carried out independent of the treatment. Separately for this study patients fill out questions about decisional conflict, participation in mental health treatment, shared decision making and the working alliance with the clinician. This results are not visible at patient level during intake and treatment. Data collection is conducted by independent research assistants. This approach diminishes undesired influence of the research team or clinicians on the results, reduces the chance of social desirable answers and enhances uniformity and quality of the collected data. Only the outcome parameters no-show, drop-out and clinical outcome (ROM) will be collected in the context of treatment.

The third strength of the study is that at T1, both the patients and clinicians are invited to complete a questionnaire about decisional conflict and shared decision making. If there are different views between patients and clinicians about the application of shared decision making, they will be detected and further analysed.

Finally, the study is conducted in four departments working in two regions and treating different diagnostic groups (depression, anxiety and personality disorders). Because the data collection takes place in real world clinical practice and in several departments the results will be generalizable to a broader group of mental health care teams, clinicians and patients with depression, anxiety and personality disorders.

The study brings about some limitations that could influence the results. First, the clinicians are not blinded for the design. It is possible that clinicians, working in the control teams, make additional efforts to stimulate patient participation, to improve the quality of the working alliance and to applicate shared decision making. Although, the research assistants are partially blinded for the study arm, they are less likely to influence the results, because the outcome parameters are measured

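### The patient–clinician comparison uses independent t-tests on ratings that are paired within dyads and clustered by clinician, so its standard error is wrong in an unknown direction and it cannot show agreement

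*Protocol*

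**What the plan says.** All references are to the protocol.

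- **Test.** Statistical analyses names what is compared, "The patients' and clinicians' views on the Shared Decision Making process (SDM-Q-9", then the VAS, and says how: "and Decisional Conflict (VAS) will be compared using independent t-tests". The same section tests the hypotheses by multilevel analysis because of the cluster randomisation, but does not extend that to this comparison.
- **Who rates what.** Under Study flow, at T1 "clinicians answer questions about shared decision making regarding their patients". Under Secondary outcome measures, for the SDM-Q-9: "At T1 clinicians will complete the same questions regarding the consultations with their patients". Under Primary outcome measure, "at T1 both patients and clinicians fill out a Visual Analogue Scale (VAS".
- **Purpose.** Primary outcome measure gives the aim of the VAS: "To compare the degree of decisional conflict (or agreement) between patients and clinicians about the decisions made". The Discussion lists the dual ratings as the study's third strength and adds: "If there are different views between patients and clinicians about the application of shared decision making, they will be detected and further analysed".

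No paired test, dyadic model or agreement statistic is named for this comparison.

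**The concern.** The independent t-test assumes two unrelated samples of mutually independent observations. Neither part of that assumption fits.

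1. A clinician score belongs to a particular patient, and the two scores describe the same intake and its decisions. They will probably be correlated.
2. The intakes are done by teams of clinicians averaging 22 study patients per team, so a clinician will commonly contribute several scores. Scores from one clinician share that clinician's way of rating.

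The first omission inflates the standard error if the correlation is positive; the second deflates it. Confidence intervals and p-values could therefore err either way.

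There is also a mismatch with the aim. A difference between two group means takes no account of which patient belongs to which clinician. Reassigning the clinician scores at random among patients leaves the independent t-test result exactly the same, although it destroys any agreement. Equal means are thus compatible with complete disagreement within dyads.

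**Working it through.** **Inputs from the protocol.** The sample size section gives 77 evaluable patients per arm, so at most 154 dyads if every clinician responds, with 22 patients included per team. It gives α = 0.05; sidedness is not stated and I take two-sided. It states no standard error, power or sample size for the patient–clinician comparison, so there is no figure to reproduce. Its own power statement, "and 65 patients per arm will yield a power of 0.80", concerns the between-arm test.

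**Assumed inputs.** Within-dyad correlation ρ (0.2–0.5 as the main range); patients per clinician m (4 or 8, that is 22/4 = 5.5 or 22/8 = 2.75 clinicians per team); intraclass correlation of clinician ratings (ICC, 0.1–0.3); equal SDs for patients and clinicians; no clinician clustering in the patients' own scores. With n dyads and common standard deviation SD:

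- variance of the mean difference assumed by the independent t-test: 2·SD²/n
- true variance with pairing only: 2(1−ρ)·SD²/n
- true variance with pairing and clinician clustering: [2(1−ρ) + (m−1)·ICC]·SD²/n

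**Step 1: pairing only.** Reported SE / true SE = 1/√(1−ρ). True size = 2[1−Φ(1.96/√(1−ρ))].

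| ρ | Reported / true SE | True size at nominal 5% |
|---|---|---|
| −0.2 | 0.91 | 7.4% |
| 0 | 1.00 | 5.0% |
| 0.2 | 1.12 | 2.8% |
| 0.3 | 1.20 | 1.9% |
| 0.5 | 1.41 | 0.6% |

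In simulation (20,000 runs, 154 dyads, no clinician clustering), power for a mean difference of 0.25 SD at ρ = 0.3 is 0.60 for the independent test and 0.74 for a paired test. At ρ = 0.5 it is 0.63 against 0.87.

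**Step 2: add clinician clustering.** True SE / reported SE = √{[2(1−ρ) + (m−1)·ICC]/2}.

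For ρ = 0.3, m = 8:
- ICC 0.1: √[(1.4 + 0.7)/2] = √1.05 = 1.03 (1.025 to three decimals); size 5.6%
- ICC 0.3: √[(1.4 + 2.1)/2] = √1.75 = 1.32; size 14%

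| ρ | m | True / reported SE, ICC 0.1 | True / reported SE, ICC 0.3 |
|---|---|---|---|
| 0.3 | 4 | 0.92 | 1.07 |
| 0.3 | 8 | 1.03 | 1.32 |
| 0.5 | 4 | 0.81 | 0.98 |
| 0.5 | 8 | 0.92 | 1.25 |

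The two errors cancel when (m−1)·ICC = 2ρ. At ρ = 0.3 that is an ICC of 0.6/7 = 0.086 with 8 patients per clinician, or 0.6/3 = 0.20 with 4. Both are ordinary values, so the sign of the net error cannot be settled without data.

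**Step 3: would a plain paired t-test do?** It uses 2(1−ρ) and still omits (m−1)·ICC. At ρ = 0.3, m = 8:
- ICC 0.1: √(2.1/1.4) = 1.22; size 2[1−Φ(1.96/1.22)] = 11%
- ICC 0.3: √(3.5/1.4) = 1.58; size 2[1−Φ(1.96/1.58)] = about 21%

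Both are further from 5% than the independent test under the same assumptions (5.6% and 14%).

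**The case against.** **The t-tests may be meant to compare arms.** The sentence can be strained to mean patients' scores by arm and clinicians' scores by arm. But its wording sets patients' views against clinicians' views, and the outcome section and the Discussion give that contrast as the purpose. A between-arm t-test would in any case ignore the team clustering for which the same section requires multilevel analysis.

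**The test is merely conservative.** A reader might infer from Step 1 that the standard error is simply 12–41% too large and that the only cost is lost power. The documents do not support this: they give no correlation and no number of patients per clinician, and Step 2 shows that plausible clustering reverses the sign.

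**A mean difference does answer part of the question.** This stands. The VAS sentence speaks of comparing degree, and a mean difference does address systematic divergence between the two parties. The choice of agreement statistic could be left to a statistical analysis plan, which was not available here. The complaint is not that a statistic is missing, but that the test actually named cannot address agreement.

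**Same consultation is partly inferred.** Also fair. The intake has two face-to-face consultations, and the SDM-Q-9 text uses the plural. The pairing needs only that a clinician's score refers to that clinician's own patient. The protocol says so directly for shared decision making; for the VAS it follows from the reference to the decisions made.

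**It is ancillary.** Agreed. Neither stated hypothesis concerns patient–clinician differences, and Table 2 labels both VAS measures as additional. The third strength in the Discussion is that both parties are asked, not the t-test.

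**Conclusion.** The protocol names a test that does not fit the data it describes. The ratings are paired within dyads and, where clinicians rate several patients, clustered by clinician. The independent t-test allows for neither, so its standard error is right only if the two errors happen to cancel or are both absent.

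The size rests on assumed inputs. Pairing alone overstates the standard error by 12–41% for ρ of 0.2–0.5. With 8 patients per clinician, ICC 0.1–0.3 and ρ = 0.3, the reported standard error is instead too small, the true one being 1.03–1.32 times as large. The net direction is unknown from the documents. Separately, the planned contrast of means cannot show agreement within dyads.

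A reader might go further and conclude that the trial's efficacy result is at risk. It is not: the between-arm analysis of the Decisional Conflict Scale is planned by multilevel analysis and does not use this comparison. The change should be made, but as a correction to a supporting analysis.

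**What to change.** Replace the t-test sentence with wording to this effect: at T1, the patient-minus-clinician difference in SDM-Q-9 and in VAS will be analysed for each dyad in a multilevel model with a random intercept for clinician, and dyad-level agreement will be reported as limits of agreement or an intraclass correlation.

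Two points of specification matter:

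- If both ratings are modelled jointly, the model needs a clinician-by-rater random effect. A clinician intercept shared by both ratings cancels from the patient–clinician contrast and leaves its standard error uncorrected.
- A plain paired t-test is sufficient only if each clinician rates a single patient, and even then it does not measure agreement.

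The cost is small: one sentence, somewhat more analysis work, and no new questionnaires. MLwiN, already named in the protocol, fits such models. The dataset must keep the patient–clinician link and a clinician identifier, which should be settled before the data are de-identified.
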